#### Drop-out criteria

Reasons for drop-out are complications during pregnancy as assessed by the trial physician. Women who give birth preterm (delivery before 37^th^ week of gestation) will be excluded from the GWG analysis. These and other reasons for drop-out are carefully documented.

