## Abstract

**Background:**

Recent studies suggest that excessive gestational weight gain (GWG) leads to adverse maternal and fetal outcomes including weight retention in the mother and an increased risk of childhood obesity in the offspring.

The aim of the GeliS study is to examine the effect of a lifestyle intervention programme during pregnancy to avoid excessive GWG and, hence, to reduce pregnancy and obstetric complications as well as the risk of maternal and offspring obesity.

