## Methods and design

### Study design and setting

The GeliS trial is a multicentre and multidisciplinary public health project in ten regions of Bavaria, a federal state of Germany, targeting maternal and fetal health. It is designed as a prospective, cluster-randomized, controlled, open intervention trial. We perform a paired cluster-randomization by matching five pairs of regions according to birth figures, sociodemographic and geographic criteria. Randomization is performed within these pairs and each pair is supervised by an expert centre for nutrition run by the Bavarian State Ministry of Food, Agriculture and Forestry.

Adherence to the study protocol is monitored by the Münchner Studienzentrum at the Technical University of Munich. The Münchner Studienzentrum is furthermore in charge of comprehensive data management according to current standards. The study will be conducted in accordance with the declaration of Helsinki as well as with current local regulatory requirements and laws. Written informed consent will be given by all participants. The study protocol was approved by the ethical committee of the Technical University of Munich and registered at the ClinicalTrials.gov Protocol Registration System (NCT01958307).

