#### Secondary outcomes

Secondary outcome parameters include:

– incidence of gestational diabetes (24^th^-28^th^ week of gestation, via an oral glucose tolerance test), glycosylated haemoglobin concentration (30^th^-34^th^ week of gestation),

– other pregnancy complications such as preeclampsia,

– anthropometric measures and health status of the newborns (birth weight, height, head circumference, LGA, small for gestational age (SGA), APGAR-Score, pH),

– obstetric complications (mode of delivery, induction of labour, rate of caesarean sections etc.),

– maternal dietary and physical activity habits during pregnancy and after delivery,

– maternal body weight after delivery (6-8 weeks postpartum),

– maternal mental health and post natal depression.

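### Pregnancy complications are both a reason for drop-out, at the judgement of a physician who can know the arm, and secondary outcomes; the protocol must separate ending the counselling from leaving the study

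*Protocol article*

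**What the plan says.** All references are to the protocol article.

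- **Drop-out criteria:** "Reasons for drop-out are complications during pregnancy as assessed by the trial physician". No list of complications or threshold is given. The section continues: "Women who give birth preterm (delivery before 37^th^ week of gestation) will be excluded from the GWG analysis". It closes: "These and other reasons for drop-out are carefully documented".
- **Secondary outcomes:** gestational diabetes (GDM) and "other pregnancy complications such as preeclampsia" are listed, with separate entries for obstetric complications and newborn measures. The Abstract makes it part of the aim "to reduce pregnancy and obstetric complications as well as the risk of maternal and offspring obesity".
- **Study design and setting:** the trial is a "prospective, cluster-randomized, controlled, open intervention trial", randomised by region within five matched pairs.
- **Power calculation:** 1900 women are needed. This is raised to 2500 to cover imbalance between the groups and drop-out of up to 25% before delivery.
- **Weight measurements, documentation of pregnancy and obstetric complications:** complications are entered in the maternity card at antenatal visits. Practice staff copy the cards and birth records at the first postnatal visit. GWG uses the weight at the last prenatal visit.
- **OGTT and HbA1c:** women diagnosed with GDM are treated at the gynaecologist's discretion, and HbA1c at weeks 30 to 34 is meant to inform on the severity of diagnosed GDM.

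**The concern.** An event that the trial counts as an outcome should not also decide whether a woman remains in the trial. Here it can, and the decision is left to the judgement of a physician who can know the arm, since the trial is open and whole regions are allocated.

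Two consequences follow if dropped women do not contribute data. First, complication rates are understated, even when both arms drop women equally. Second, if the readiness to drop differs by arm, a difference in rates can appear with no true effect, or a true one can be hidden. There is a plausible reason why it might differ. Exclusion criteria ties high-risk pregnancy to contraindications to exercise, and only intervention women receive individual advice on physical activity (Control group). This is an inference, not something the protocol states.

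Outcomes that arise after the drop-out are also at risk: final GWG, mode of delivery, birth weight and size for gestational age.

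**Working it through.** **1. What drop-out means in this document.** Two places bear on it. Drop-out criteria counts an exclusion from analysis (preterm birth) among the reasons for drop-out. Power calculation enlarges the sample to replace drop-outs:

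- Plan's figure before drop-out: 40% against 30%, power 90%, alpha 0.05 (two-sided assumed) gives 477 per arm, 954 in total; with continuity correction 496 per arm, 992 in total.
- Design effect with 10 regions of 190 women and an intraclass correlation of 0.005: 1 + (190 − 1) × 0.005 = 1.945.
- 954 × 1.945 = 1856 and 992 × 1.945 = 1929. Both are within 3% of the stated 1900.
- Allowance: 1900 / 0.75 = 2533, and 2500 × 0.75 = 1875. The stated 2500 is within 3% of the former.

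The sample size therefore reproduces and is not disputed. The allowance treats a drop-out as a woman who adds nothing to the comparison. The preterm exclusion is limited to the GWG analysis; the complication rule carries no such limit.

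**2. Sections side by side.** Drop-out criteria lets a complication end participation. The sections on weight measurements and documentation, and on OGTT and HbA1c, expect complications to be retrieved after birth and women with GDM to be present at weeks 30 to 34. These fit together only if some affected women stay and others are dropped. The protocol does not say which, or what happens to the data of those dropped.

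**3. Direction and possible size.** Let i be the true incidence and d the fraction of affected women dropped and not analysed, with no unaffected women dropped. Then

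observed incidence = i(1 − d) / (1 − i·d).

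All values of i and d below are assumptions; the documents give none.

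- i = 10%, d = 30%: 0.07 / 0.97 = 7.2%.
- i = 10%, d = 10%: 0.09 / 0.99 = 9.1%.
- Ratio 0.0722 / 0.0909 = 0.79, or 1.26 if the arms are reversed.
- i = 2%, same d: 0.014 / 0.994 = 1.41% and 0.018 / 0.998 = 1.80%, ratio 0.78.
- i = 10%, d = 50% against 25%: 0.05 / 0.95 = 5.3% and 0.075 / 0.975 = 7.7%, ratio 0.68 (1.46 reversed).
- Equal d = 30% at i = 10%: both arms show 7.2% instead of 10%, about 28% too low, and the ratio stays at 1.
- Equal d = 50% with true rates of 8% and 10%: 0.04 / 0.96 = 4.2% and 0.05 / 0.95 = 5.3%. The difference falls from 2.0 to 1.1 points, while the ratio barely moves (0.80 to 0.79).

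Equal dropping thus mainly distorts rates and differences in rates. Unequal dropping distorts the ratio as well, and the distortion depends little on the incidence.

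**The case against.** The strongest reply is that the protocol nowhere says that dropped women go unanalysed. Its only explicit analysis exclusion is preterm birth, for GWG alone, and follow-up of drop-outs is often left to the full protocol or the analysis plan. It is true that the loss is a reading and not a quotation. But the point does not rest on silence. The article states a rule that conflicts with its own outcomes and with its own data-collection sections, and an analysis plan cannot recover data that a drop-out rule stops from being collected.

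Several stronger readings are tempting and are not supported:

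- *Every woman with a complication is removed.* The rule reaches only those whom the physician drops, and the documentation and OGTT sections expect others to stay.
- *Obstetric complications trigger drop-out.* Caesarean section, induction and mode of delivery belong to the delivery and cannot be the complication in pregnancy that ends participation. They can only be lost as a consequence.
- *The primary outcome is lost because complications are linked to weight gain.* A link does not make a weight missing. GWG is lost only if data collection stops at drop-out, because the last prenatal weight is then not retrieved. If it does stop, the association between excessive GWG and complications described in the Discussion means that the loss may well be informative.
- *Up to 25% of women may be removed this way.* That allowance covers drop-out for any reason, and the enlargement also covers imbalance between the groups.
- *Dropping does differ by arm.* Nothing in the document shows this; control data are collected at the same time periods.

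It may also be said that a complication is recorded before the woman leaves, since reasons for drop-out are documented. That could rescue the count of the triggering event, but not the later outcomes.

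**Conclusion.** The point holds in a limited form. Pregnancy complications are at once secondary outcomes and a discretionary ground for drop-out in an open trial, and the sections that expect affected women to stay must be reconciled with the drop-out rule. As written, women whom the physician drops are naturally read as lost to the comparison, so removal after randomisation depends on the outcome.

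The secondary complication outcomes are exposed first. GWG and the delivery and newborn outcomes are exposed if data collection ends at drop-out. The size cannot be derived from the documents. Under the assumed rates above, unequal dropping gives spurious risk ratios between 0.68 and 0.79 (1.26 to 1.46 with the arms reversed); with equal dropping no spurious ratio arises, but the rates are too low. These figures assume that dropped women are not analysed and that only affected women are dropped.

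**What to change.** Amend Drop-out criteria so that the end of counselling and the end of study participation are two different things:

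1. Whether a complication ends the counselling is a clinical decision and is not judged here. State that it does not end study participation.
2. Collect the maternity card and birth record for every woman who has not withdrawn consent.
3. Analyse her in her randomised region for all secondary outcomes. Include her in the GWG analysis where a final prenatal weight exists and the protocol's preterm exclusion does not apply.
4. Report the number of drop-outs and their reasons by arm.
5. Reconcile the amended section with the sections on documentation of complications and on OGTT and HbA1c.

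The cost is a short amendment and a little more data retrieval, since copying these records is already planned. It should be made while the data can still be collected, because records never retrieved cannot be reliably reconstructed at analysis.

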#### Counsellor recruitment and qualification

All practice-based gynaecologists including their medical staff as well as all midwives in the selected regions are contacted via information leaflets and by phone. Participating gynaecologists, medical staff or midwives will act as local health care providers and key communicators by implementing counselling sessions for participating pregnant women in the “real-life” setting of routine care. They have to attend a standardised qualifying seminar to ensure competency in lifestyle counselling and standardisation of the intervention. Seminar and information material for the counsellors as well as for the pregnant women were developed in cooperation with the network “Healthy Start - Young Family Network”, a project of IN FORM, which is funded by the German Federal Ministry of Food and Agriculture [48].

#### Participant recruitment

Before the 12^th^ week of gestation, all pregnant women consecutively presenting in the participating practices are invited by midwives or medical staff to take part in the study. To check inclusion and exclusion criteria and to obtain basic information, participating as well as non-participating women are requested to fill in a short screening questionnaire which includes demographic and anamnestic data relevant to the study. If women fulfill all criteria and are interested to participate, they receive detailed information about the study as well as a form to provide their written informed consent. All these materials were approved by the ethical committee.

### The lifestyle intervention programme

The intervention programme consists of four structured and partially individualised counselling sessions emphasizing diet, physical activity and weight monitoring (12^th^-16^th^, 16^th^-20^th^, and 30^th^-34^th^ week of gestation and 6^th^-8^th^ week postpartum). The counselling sessions are exclusively given by specifically trained and certified midwives, gynaecologists or medical staff alongside routine prenatal visits and follow a defined curriculum. Pregnant women receive a pedometer and brochures including examples for adequate exercise and a list of local prenatal physical exercise programmes as well as recommendations for a balanced diet in pregnancy according to the above mentioned recommendations on nutrition in pregnancy [49]. Furthermore, they receive a weight gain chart according to their baseline BMI category for self-monitoring of weight development as proposed by the IOM [16]. Figure 1 shows the study scheme including all visits, examinations and other procedures as well as the data that is taken from the pregnant women/mothers and their newborns.

**Figure 1 F1:**
[figure not shown]
Study scheme of the GeliS study.

*Visit 0* (≤ 12^th^ week of gestation) represents the screening examination. After checking inclusion and exclusion criteria and obtaining written informed consent, each participant obtains a folder containing questionnaires (on dietary habits and supplements/physical activity/maternal mental health) as well as a pedometer (Beurer GmbH, Ulm, Germany) with adequate instructions.

*Visit 1* (12^th^-16^th^ week of gestation): Detailed information about healthy diet and physical activity in pregnancy is given in a face-to-face session of 30 to 45 min. duration. The importance of a healthy lifestyle during pregnancy and its determining factors are explained. Pregnant women learn to handle the principles of healthy eating and to understand the risks of alcohol, smoking and foodborne infections during pregnancy. Further advice relates to GWG, weight monitoring and to critical nutrients in pregnancy (folic acid, iodine, and iron). A list of adequate prenatal physical exercise programmes, brochures including recommendations for a balanced diet in pregnancy as well as a chart for adequate weight gain according to baseline BMI category to self-monitor weight development are handed out. The questionnaires distributed in *Visit 0* are collected.

*Visit 2* (16^th^-20^th^ week of gestation, 4 weeks distance between the two visits): Specific and detailed individual counselling targeting dietary habits and physical activity also considering the information from the first set of questionnaires is given. Moreover, women are motivated to participate in a standardised two hour oral glucose tolerance test (OGTT) between the 24^th^ and 28^th^ week of gestation, and an appointment for the OGTT is fixed.

*Visit 3* (30^th^-34^th^ week of gestation): Repetition and consolidation of contents from the previous visits, with an emphasis on weight monitoring. Counsellors provide information on prenatal maternity courses, post natal exercise classes and on specific problems, such as water retention or back complaints. In addition, the importance of breastfeeding is addressed. A venous EDTA blood sample for measurement of glycosylated haemoglobin (HbA1c) is collected. The second set of questionnaires is handed out.

*Visit 4* (6^th^-8^th^ week postpartum): The fourth counselling session includes dietary advice during breastfeeding and information on infant feeding principles. Full breastfeeding is recommended at least up to the age of 4 months. If not returned yet, the second set of questionnaires is collected and the third set of questionnaires (dietary habits and intake of supplements/physical activity/post natal depression/evaluation) is handed out together with a free envelope to return the questionnaires. Maternal weight is measured and documented at each visit.

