**Methods and design:**

The GeliS study is a multicentre cluster-randomized controlled trial. A total number of 2500 pregnant women (singleton pregnancy) with a pre-pregnancy BMI ≥ 18.5 kg/m^2^ and ≤ 40 kg/m^2^ will be recruited in practices of gynaecologists and midwives in ten Bavarian regions. The intervention comprises three structured and individualised counselling sessions on a healthy diet, regular physical activity as well as weight monitoring during pregnancy and one session after delivery, respectively. The counselling sessions are attached to routine pre- and postnatal visits using standardised materials and procedures. In the control regions, general recommendations for a healthy lifestyle are given. An oral glucose tolerance test is offered to all participants.

The primary outcome is the proportion of participants with excessive GWG. Secondary outcomes include pregnancy and obstetric complications such as frequency of gestational diabetes, preeclampsia and caesarean sections as well as weight retention in the mothers and BMI and other health variables in the offspring. A 5-year follow-up of both mothers and their infants is planned.

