### Control group

Participants in the control group receive standard prenatal care, including a leaflet about a healthy lifestyle in pregnancy, but no specific individual advice on diet, physical activity or weight gain in pregnancy is given. Data collection and distribution of questionnaires take place within routine prenatal care visits at the same time periods as in the intervention group.

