#### OGTT and HbA1c

To test for gestational diabetes mellitus (GDM), a standardised two-hour oral glucose tolerance test (OGTT) is offered to all participants between the 24^th^ and 28^th^ week of gestation. Tests are performed by the participating gynaecological practices according to the 2011 guidelines of the German Diabetes Society (DDG) and the German Society of Gynaecology and Obstetrics (DGGG) [54] which is in line with the guidelines of the International Association of the Diabetes and Pregnancy Study Groups (IADPSG) [55]. After an overnight fast, serum glucose level is measured before, one and two hours after intake of 75 grams glucose (Dextro®OGT, Roche, Mannheim). Treatment will be performed at the discretion of the participating gynaecologist. Every participating gynaecological practice will receive information about the DDG/DGGG guidelines for the management of gestational diabetes [54] and is asked to consider these principles as soon as GDM is diagnosed.

To obtain additional information on the presence and severity of diagnosed GDM, EDTA blood is collected for the measurement of the glycosylated haemoglobin concentration between the 30^th^ and 34^th^ week of gestation.

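### The text describes encouragement and booking for the OGTT only in the intervention programme, so test uptake, and with it the GDM comparison (a secondary outcome), may differ by arm

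*Protocol article*

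**What the plan says.** The visit descriptions stand under The lifestyle intervention programme, which opens: "The intervention programme consists of four structured and partially individualised counselling sessions emphasizing diet, physical activity and weight monitoring". Visit 2 (weeks 16 to 20) is one of those sessions. After the individual counselling content, it says that "women are motivated to participate in a standardised two hour oral glucose tolerance test (OGTT", with the test due in weeks 24 to 28, "and an appointment for the OGTT is fixed".

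The Control group section reads: "Participants in the control group receive standard prenatal care, including a leaflet about a healthy lifestyle in pregnancy". It excludes specific individual advice on diet, activity or weight gain, and adds: "Data collection and distribution of questionnaires take place within routine prenatal care visits at the same time periods as in the intervention group". It does not mention the OGTT.

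Two statements about the test cover both arms. The abstract has "An oral glucose tolerance test is offered to all participants", and the section OGTT and HbA1c has "a standardised two-hour oral glucose tolerance test (OGTT) is offered to all participants". That section also sets one procedure, one time window and one guideline, with testing by the participating practices.

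Under Secondary outcomes, GDM incidence is listed first and is determined "via an oral glucose tolerance test". Study design and setting describes the trial as open.

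**The concern.** A woman who does not take the test cannot be found to have GDM by the stated method, so observed incidence depends on who is tested. If one arm receives persuasion and a booked appointment and the other receives only an offer, the intensity of case finding is tied to allocation. In an open trial, blinding does not offset this.

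The outcome matters to the trial's message. The Background reports a trend towards less GDM in the pilot, and the Discussion says most earlier small studies were not adequately powered for it. Extra detection in the intervention arm would tend to hide the benefit the trial hopes to show.

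**Working it through.** **1. Is the step arm-specific in the text?**

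| Element | Intervention | Control |
|---|---|---|
| Test offered | Yes (abstract; OGTT and HbA1c) | Yes (same statements) |
| Test, window, criteria | Common | Common |
| Encouragement to attend | Yes (Visit 2) | Not stated |
| Appointment fixed | Yes (Visit 2) | Not stated |
| Timing of data collection | Visit schedule | Same periods, at routine visits |

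Where parity is intended for other measures, the article says so: questionnaire timing (Control group), food frequency questionnaires at the same time points (Dietary assessment), and activity assessment in both groups (Physical activity assessment). For the OGTT, parity is stated for the offer and the method, but not for the route to the test.

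**2. Inputs for size.** The article gives no OGTT uptake, GDM rate or GDM power, so there is no plan figure to reproduce; the power calculation concerns excessive weight gain only. The uptakes below, and the 10% true incidence, are assumptions.

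**3. Untested women counted as non-cases.** Let p be the true incidence in both arms, and u_I and u_C the uptakes, with testing unrelated to risk.

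Observed rate = p × u, so observed risk ratio = (p × u_I)/(p × u_C) = u_I/u_C. The incidence cancels. A true risk ratio of u_C/u_I would be masked completely.

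| Assumed uptake, I vs C | Spurious risk ratio | True risk ratio fully masked | Observed rates if p = 10% |
|---|---|---|---|
| 95% vs 90% | 0.95/0.90 = 1.06 | 0.90/0.95 = 0.95 | 9.5% vs 9.0% |
| 90% vs 80% | 0.90/0.80 = 1.13 | 0.80/0.90 = 0.89 | 9.0% vs 8.0% |
| 90% vs 70% | 0.90/0.70 = 1.29 | 0.70/0.90 = 0.78 | 9.0% vs 7.0% |

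Equal uptake gives a ratio of 1.00 at any level.

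**4. Only tested women analysed.** Let k be the incidence among tested women divided by the incidence among all women in that arm. With no true effect, the observed ratio is k_I/k_C. This is 1.00 at any uptake if testing is unrelated to risk (k = 1 in both arms). It departs from 1 if the encouragement changes which women attend. The article gives nothing from which to put a size or a direction on this.

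**5. Reach into the primary outcome.** In the widest case above, 9.0% − 7.0% = 2 percentage points more intervention women are diagnosed. Suppose their treatment prevented every excessive weight gain among them, at the 40% control rate in the power calculation. The contrast would then move by 0.02 × 0.40 = 0.8 percentage points, against a planned difference of 40% − 30% = 10 points.

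**The case against.** The strongest reply is that the asymmetry is inferred from silence. The visit descriptions also carry procedures common to the whole trial: screening and consent, questionnaires for each participant, weight at each visit, and the HbA1c sample at Visit 3. HbA1c is a trial outcome, so its appearance there cannot mean that controls are not sampled, and the OGTT booking might likewise be common. Figure 1 is not available here, and an article condenses a fuller protocol. This stands to the extent that unequal encouragement is the natural reading but not a certain one. The wording about motivating women sits beside counselling content, and the Control group section extends only data collection and questionnaire timing to controls.

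The reply also notes that the ratios in step 3 need untested women in the denominator as non-cases, which the article does not specify. That stands too. The choice of denominator may be in an analysis plan that is not shown, and its absence is no fault here. It does not dispose of the point, because restricting to tested women replaces one route to bias with another.

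A reader might infer more than the article supports:

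- **GDM is measured differently in the two arms.** It is not; only the route to the test may differ.
- **HbA1c and later weight gain carry the same bias.** If extra testing leads to treatment that changes them, that is a consequence of the allocated programme, not detection bias.
- **Making GDM among tested women the main estimate would cure the problem.** That choice conditions on an event after randomisation and is itself debatable.
- **The bias is as large as a plausible real effect.** The article gives no GDM effect size for such a comparison.

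**Conclusion.** The point holds as a moderate one, confined to a secondary outcome. As written, the plan gives intervention women an extra push towards an optional test that determines GDM, and states no equivalent for controls. If uptake differs as a result, the comparison is distorted. With untested women counted as non-cases, the bias runs against the intervention, so it is more likely to hide a benefit than to create one. With tested women only, the direction cannot be stated.

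The size is unknown. The range of 1.06 to 1.29 rests on assumed uptakes, on equal true incidence, on testing unrelated to risk, and on untested women being counted as non-cases. If uptake is nearly complete in both arms, little bias remains. The primary outcome is not materially affected.

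**What to change.** Use the same OGTT invitation and the same appointment step in control practices, at the routine visit in the 16 to 20 week window, where control data are already collected. If this is already done, say so in the Control group section. Report OGTT uptake by arm. Add a sensitivity analysis of GDM incidence that imputes or weights for untested women using baseline covariates such as BMI and age.

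The procedural step is the main remedy and belongs before or during recruitment, because analysis can only partly repair unequal uptake. The cost is about one line in the control-region procedure and a small addition to the analysis. The downside is that control care moves slightly away from pure routine, for a test the plan already offers to everyone.
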